### Intervention

An extended multidisciplinary assessment starts with a visit to the geriatric outpatient clinic. A multifactorial fall risk assessment will be conducted aiming to identify modifiable fall risk factors. The assessment of fall risk factors and design of the treatment plan is based on the directives in the CBO guideline "Prevention of fall incidents in older persons" [25]. The assessment consists of a general medical and drug history, a fall and mobility history and physical examination. According to the recommendations of the CBO guideline special emphasis is placed on signs and symptoms of potentially modifiable fall and fracture risk factors such as postural hypotension, visual impairment, parkinsonism, osteoporosis, osteoarthritis, gait disorders, psychotropic and cardiac drug use, and environmental hazards. When indicated, additional diagnostic tests can be performed (e.g. laboratory tests or imaging). Based on the assessment of risk factors an individually tailored treatment regimen aimed at reduction of the fall risk is composed in close collaboration with the general practitioner of the participant. In the Netherlands, the general practitioner has a central role in the coordination of specialist's care, home care and physiotherapy among others. The collaboration facilitates the transmural continuity of care that has been lacking in most previously performed fall risk reduction trials. The multifactorial treatment can consist of, for example, withdrawal of psychotropic drugs, balance and strength exercises by a physical therapist, home hazard reduction by an occupational therapist or referral to an ophthalmologist or cardiologist. Per participant and per diagnosis the International Classification of Diseases code (ICD10) code and recommendations are reported to document the treatment regimen.

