### Procedure

All persons who consult the emergency department or primary care physician after a fall receive usual care. Within two weeks after the initial presentation, written information is sent and several days thereafter, the potential participants are contacted by telephone. All actual participants (who sign informed consent) are visited at their homes by a trained interviewer within 3 months after the fall incident. During the first home visit, the fall risk profile [16], fall history, independence in activities of daily living, quality of life and physical performance are measured. All high-risk participants will report falls during at least one year using a fall calendar and receive a cost-evaluation questionnaire at 3, 6 and 12 months after the first home visit. The times to first and second fall are the primary outcome measures. One year after the first home visit, they are visited a second time to reassess the activities of daily living, quality of life and physical performance. Scores on these questionnaires and tests are used as secondary outcome measures. Furthermore, the treatment adherence and medication use are evaluated. Table 1 presents an overview of the procedure and measurements. The measurements used are described later on in this article.

**Table 1 T1:** Overview of procedure and measurements

	Months	Measurements	Purpose
1st home visit	0	fall risk profile	selection high risk participants
		fall history	assessment of fall risk factors, confounders
		activities of daily living	secondary outcome measure
		quality of life	secondary outcome measure
		medication use	assessment of fall risk factors
		medical history	assessment of fall risk factors, confounders
		physical performance	secondary outcome measure
1st follow-up	3	1st calendar sheet	primary outcome measure
		3 months cost-evaluation	primary outcome measure
2nd follow-up	6	2nd calendar sheet	primary outcome measure
		6 months cost-evaluation	primary outcome measure
3rd follow-up	9	3rd calendar sheet	primary outcome measure
2nd home visit	12	activities of daily living	secondary outcome measure
		quality of life	secondary outcome measure
		medication use	treatment adherence
		medical history	secondary outcome measure, confounders
		physical performance	secondary outcome measure
		treatment adherence	confounder, to enhance the interpretation of the results
4th follow-up	12	4th calendar sheet	primary outcome measure
		12 months cost-evaluation	primary outcome measure

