Fall history is assessed with the fall history instrument (Carefall Triage Instrument, version 007), which is a questionnaire developed by the Academic Medical Center, the VU University Medical Center and the Erasmus Medical Center, The Netherlands. The fall history collects data on the circumstances of the last and previous falls, mobility and risk factors of bone loss and osteoporosis, social status and general health. Medical history is assessed using a questionnaire on self-reported (chronic) diseases both in the past and present. The questionnaire includes 7 major chronic diseases, i.e. chronic lung diseases, cardiac diseases, vascular diseases, stroke, diabetes mellitus, malignant neoplasms and joint disorders (i.e. osteoarthritis and rheumatoid arthritis). In addition, participants are asked to indicate any other chronic disease, including psychological diseases, which they have or have had. Medication use is assessed by directly copying the names of drugs used in the previous two weeks from the containers. The name, doses per unit, number of times taken per day, time of administration, doses per intake, purpose, prescription or over the counter (OTC) and whether the drug has been prescribed after the fall are assessed for each drug. This information is compared to medication records of the public pharmacy. Level of independence in activities of daily living (ADL) will be examined using the Barthel Index (range 0, fully dependent, to 20, fully independent) [33]. The level of functioning on more complex daily activities will be examined using a scale of instrumental ADL introduced by Lawton and Brody (range 0, fully dependent, to 8, fully independent) [34]. Quality of Life (QoL) is examined using the Dutch translations of the SF-12 and the EQ-5D. The SF-12 consists of 12 items and is a abbreviated version of the SF-36 [35]. The SF-12 has been designed and validated to measure health related QoL in large population studies [35,36]. The EQ-5D (EuroQol) has been developed to generate a general index of experienced health and for the assessment of Quality Adjusted Life Years (QALY). It is therefore suitable for economic evaluations [37]. The assessment consists of 5 items (mobility, self-care, usual activities, pain/discomfort and anxiety/depression) and a visual analogue scale (0, worst, to 100, best imaginable health state) [37]. The fall history, ADL and QoL questionnaires are sent to the participants prior to the first home visit. Participants are asked to complete these questionnaires before the home visit. The visiting researcher assists participants who are unable to complete these questionnaires independently.

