#### Follow-up

At the first home visit the participants receive a fall calendar [16]. For the period of one year, the participants tick per week whether they did or did not fall during that week. A fall is defined as an unintentional change in position resulting in coming to rest at a lower level or on the ground [41]. Once per 3 months the participants return a calendar sheet by mail. When no sheet is received, or when the sheet is completed incorrectly, we inquire by telephone whether, and if yes, when the participant has fallen in the past 3 months.

The cost-evaluation questionnaire registers the costs made to prevent a new fall or the consequences of a new fall. The questionnaire assesses: the number of visits to physicians, therapists or day care centres; amount and aim of surgical procedures; number of days of admission to a hospital, home or nursing home; purchase of aids and adaptations in the home environment. The questionnaires are conducted 3, 6 and 12 months after the first home visit. The 3 and 6 months questionnaires are sent by mail and apply to the preceding 3 months. The 12 months questionnaire is assessed during the interview of the second home visit. This questionnaire applies to the preceding 6 months. When no questionnaire is received, or when it is completed incorrectly, the questionnaire will be completed by telephone.

During the second home visit, one year after the first visit, the same physical performance tests are conducted along with a reassessment of fall related healthcare costs, medical history, medication use, quality of life and activities of daily living. In addition, in the intervention group, adherence to the treatment regimen is evaluated. Treatment adherence in the intervention group is evaluated per recommendation given. Recommendations regarding changes in medication are evaluated by reassessing the medication use as described above. Adherence to all other recommendations (such as referrals to physical therapy or cardiologist) is assessed by asking whether, to what extent, and how the recommendations of the intervention were effected. The information from the participant is completed with information from the rapports of the involved specialists.

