### Statistics

Data will be primarily analysed according to the intention-to-treat principle, i.e., including all randomized participants, regardless of whether they received or did not receive the intervention. Subsequently, the results of the intention-to-treat analysis will be compared with the results of an on-treatment analysis.

At baseline, differences in baseline characteristics will be compared between the intervention and control group to examine comparability between the two groups.

To examine the effectiveness of the multidisciplinary transmural care, Cox proportional hazards regression will be conducted, with time to first fall and time to second fall within one year of follow-up as outcome measures, and with age, gender and living situation as covariables. Subsequently, multiple linear regression analyses will be used to compare differences in secondary outcome measures (ADL-score, QoL, physical performance and morbidity data) at 12 months follow-up between intervention and control group.

The economic evaluation will be conducted from a societal perspective, which implies that all costs and outcomes are taken into account. The economic evaluation will involve calculating cost-effectiveness and cost-utility ratios. The incremental costs and effects of the intervention will be compared with usual care. The difference in costs of the intervention group and usual care group will be computed using bootstrapping techniques. Uncertainty ratios will be presented on cost effectiveness and cost utility planes. Acceptability curves will also be estimated. These present the probability that the intervention is cost-effective given a ceiling ratio that policy makers are willing to invest.

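### Admissions are recorded only in relation to falls and death is not an outcome, so an intervention that can withdraw psychotropic drugs is not compared with usual care on non-fall admissions or deaths

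*Protocol article*

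**What the plan says.** **Intervention.** The Intervention section of the protocol article states: "The multifactorial treatment can consist of, for example, withdrawal of psychotropic drugs, balance and strength exercises by a physical therapist". The assessment puts emphasis on, among other things, "gait disorders, psychotropic and cardiac drug use, and environmental hazards". Participants are 65 or older and at high risk of recurrent falling.

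**Outcomes.** The Procedure section says "The times to first and second fall are the primary outcome measures"; Table 1 there also labels the cost evaluation as primary. The Statistics section plans regression comparisons of "secondary outcome measures (ADL-score, QoL, physical performance and morbidity data) at 12 months follow-up between intervention and control group". Table 1 gives the month-12 medical history the purpose "secondary outcome measure, confounders", and the Baseline assessment section describes the instrument: "Medical history is assessed using a questionnaire on self-reported (chronic) diseases both in the past and present". It covers seven major chronic diseases, cardiac disease and stroke among them, plus any other chronic disease, psychological ones included.

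**Admissions.** Days spent in hospital, a home or a nursing home are one item of the cost questionnaire at months 3, 6 and 12. The Follow-up section sets its scope: "The cost-evaluation questionnaire registers the costs made to prevent a new fall or the consequences of a new fall". The same section describes the month-12 reassessment of costs as one of fall-related healthcare costs.

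**Economic perspective.** The Statistics section adopts a societal perspective and says this means counting every cost and every outcome.

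Death and any-cause admission are not named as outcomes anywhere in the article.

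**The concern.** Stopping a psychotropic drug can have effects unrelated to falling. An admission for psychiatric relapse, or for any other non-fall reason, lies outside the stated scope of the one form that asks about admissions. A death is not an event in any planned comparison.

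The Abstract and the Discussion both look ahead to wider use of the programme if it works. A lower hazard of falling is one part of that decision; whether participants in either arm were admitted or died more often is another. Deaths also matter for reading the fall result itself, because someone who has died can no longer fall. A separate consequence is that a cost analysis fed only by fall-related resource use cannot deliver the societal perspective it claims.

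**Working it through.** **1. What each planned measure can register**

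| Measure | Restricted to falls? | Can show worsening? | Non-fall admission | Death |
|---|---|---|---|---|
| Time to first and second fall | yes | yes, for falls | no | no |
| Cost questionnaire, months 3, 6, 12 | yes, by stated scope | yes, for fall-related use | no, if the scope is followed | no |
| ADL, SF-12, EQ-5D, physical performance, month 12 | no | yes | indirectly, in those visited | no |
| Self-reported morbidity, month 12 | no | yes, for chronic disease | not counted | no |

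The morbidity questionnaire asks about diseases past and present. A participant who takes a psychotropic drug may already report the underlying condition at baseline, so a relapse need not change the answer. The last two rows exist only for people alive and reached at month 12.

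**2. Cost scope.** The Follow-up section confines the questionnaire to new falls. The Statistics section says no cost or outcome is left out. Both cannot hold if the questionnaire is the source of the resource-use data.

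**3. The plan's own sample-size figures.** The article gives 57 per group, and 82 after 30% drop-out. The control-group rate is not stated. Assuming 50% against 25% (two-sided 0.05, power 80%, pooled two-proportion formula) gives 58, close to 57. Drop-out: 57 / 0.70 = 81.4, rounded up to 82. There is no arithmetic error here. With 100 enrolled per arm, the same 30% leaves 70.

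**4. Precision of an added by-arm comparison.** The article gives no admission or death rates, so the one-year risk p of any admission or death is an assumption, taken as equal in both arms.

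Half-width of the 95% interval for the risk difference = 1.96 × √(2p(1−p)/n)

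| Assumed p | n = 100 per arm | n = 70 per arm |
|---|---|---|
| 15% | 1.96 × √(0.255/100) = 9.9 points | 1.96 × √(0.255/70) = 11.8 points |
| 25% | 1.96 × √(0.375/100) = 12.0 points | 1.96 × √(0.375/70) = 14.3 points |
| 35% | 1.96 × √(0.455/100) = 13.2 points | 1.96 × √(0.455/70) = 15.8 points |

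**5. Power for the separate components** (two-sided 0.05, control rates assumed)

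Power = Φ{[|p₁−p₂| − 1.96√(2p̄(1−p̄)/n)] / √[(p₁(1−p₁)+p₂(1−p₂))/n]}, with p̄ the mean of p₁ and p₂.

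| Assumed change | n = 100 per arm | n = 70 per arm |
|---|---|---|
| Deaths 3% to 6% | 17% | 13% |
| Deaths 5% to 10% | 27% | 20% |
| Deaths 10% to 20% | 51% | 38% |
| Non-fall admissions 20% to 30% | 37% | 28% |
| Non-fall admissions 30% to 45% | 59% | 45% |

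This trial cannot test mortality reliably. The added outcome is worth having as an estimate with its interval, not as a test.

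**The case against.** **The outcome set is not one-sided.** A reader might infer that every stated outcome is either a measure of benefit or limited to falls. The documents do not support that. Morbidity, ADL, quality of life and physical performance are compared between arms, can move in either direction, and the morbidity questionnaire covers cardiac and psychological disease. This stands, and it narrows the point to events that those measures do not count and to people not reached at month 12.

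**Harm would not be wholly invisible.** Both arms return quarterly calendars, are telephoned when a sheet is missing, and are visited at month 12. Deaths would come to light that way. This also stands: what is absent is a declared comparison by arm, not any chance of knowing.

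**The full protocol may cover safety.** A design article commonly leaves adverse-event procedures to the full protocol, so their absence here is no finding. The point does not depend on it. It rests on two positive statements in the article: the declared outcomes and the declared scope of an existing form.

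**The admission item may be broader than its form.** The item itself carries no fall qualifier, and the questionnaire is not shown. That is fair, but the form's scope and the month-12 description both tie it to falls. If the item is in fact broader, the text needs correcting.

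**An excess of admissions would be ambiguous.** The intervention itself prompts diagnostic tests and specialist referrals, so more admissions could reflect disease being found. This stands as a caution on interpretation; it is a reason to record the cause, not to leave the events uncounted.

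**Conclusion.** The point holds in a limited form. Psychotropic withdrawal is a named component of the intervention, the only admission data are scoped to falls, and neither death nor any-cause admission is a declared outcome. Followed as written, the trial would not compare non-fall admissions or deaths by arm, and its cost data would not match its stated perspective.

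Two further inferences are tempting and unsupported. The article does not say that cardiac drugs are withdrawn; it lists cardiac drug use as something to assess. It also states no rule for declaring success, so it cannot be said that the plan would call the intervention a success despite net harm.

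The gain from the change is modest: a half-width of about 10 to 13 points at 100 per arm, or 12 to 16 at 70 per arm, for assumed one-year risks of 15% to 35%. It would show or exclude only a large harm. None of this affects the validity of the planned fall analysis, but the change is cheap enough that it should be made.

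**What to change.** - **Collect.** Widen the admission item to any-cause admission, with date and main reason, in both arms. Use the existing questionnaires, their back-up telephone calls and the month-12 visit. The recall periods of 3, 3 and 6 months already cover the year. Record date of death for all randomised participants, for example through the general practitioner.
- **Report.** Add any-cause admission or death as one secondary outcome, compared by randomised group with a 95% confidence interval. Show deaths and admissions separately as well, with the main reasons for admission.
- **Reconcile.** Make the Follow-up and Statistics sections agree on cost scope: either collect resource use beyond falls, or describe the perspective as limited to fall-related costs.

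The cost is a slightly longer form and one more comparison, with an imprecise estimate that needs careful reading given the tests and referrals in the intervention arm. No change to care is involved.

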### Usual care

Usual care in The Netherlands after a fall mainly consists of treatment of the consequences of the fall. Although the CBO guideline was released in 2004 [25], multifactorial fall risk prevention has not yet been implemented by general practitioners or at the accidents and emergency departments. In primary care settings 'usual care' only incidentally includes systematic assessment and treatment of fall risk factors.

### Measurements

#### Baseline assessment

During the first home visit, the risk of recurrent falling, fall history, medical history, medication use, independence in activities of daily living and quality of life are assessed. Risk of falling is assessed using a fall risk profile [16]. This profile, which was developed and validated in the Longitudinal Aging Study Amsterdam, [16] is used to screen participants with a high risk of recurrent falling. Recurrent falling is defined as 2 or more falls in a 6-month period [8,16,18]. This profile consists of 5 questions, 2 measurements (handgrip strength and body weight) and 2 interaction items. To measure handgrip strength a digital strain-gauged dynamometer (Takei TKK 5401, Takei Scientific Instruments Co. Ltd., Tokyo, Japan) is used. To measure body weight, a calibrated balance beam scale is used. On each item, points are scored and the scores are summed (range 0–30). Table 2 presents the diagnostic values of the risk profile for different cut off points on the fall risk score for 426 participants in the LASA-study who reported at least one fall in the previous year [16]. For this study, participants are defined at high risk of recurrent falling as the total score is 8 or higher. For an optimal combination of sensitivity and specificity, a cut-off score of 11 should be used. However, with a cut-off score of 11, a low sensitivity is obtained and too many participants with a high risk of recurrent falling will be missed. To ensure that not too many low risk participants are falsely diagnosed as high risk, the specificity should not be too low. At a cut-off score of 8, the sensitivity is higher than 50% and the specificity is higher than 70%.

**Table 2 T2:** Diagnostic values of the risk profile at different cut-off points in the total risk score

Cut-off in the total risk score	% at high risk group	Sensitivity (%)	Specificity (%)	Σ^a ^(%)	PV+ (%)	PV-	P_falls_
0 vs. ≥ 1	782	95.1	11.7	106.8	41.1	78.8	0.10 vs. 0.34
0–1 vs. ≥ 2	69.7	86.1	22.1	108.2	41.8	71.0	0.11 vs. 0.36
0–2 vs. ≥ 3	61.5	79.9	33.8	113.7	43.9	72.1	0.13 vs. 0.39
0–3 vs. ≥ 4	51.4	70.8	47.3	118.1	46.6	71.4	0.14 vs. 0.43
0–4 vs. ≥ 5	46.0	66.0	54.5	120.5	48.5	71.2	0.15 vs. 0.46
0–5 vs. ≥ 6	39.2	60.4	64.0	124.4	52.1	71.4	0.17 vs. 0.50
0–6 vs. ≥ 7	35.4	55.6	68.0	123.6	53.0	70.2	0.17 vs. 0.52
0–7 vs. ≥ 8	32.6	52.1	71.2	123.3	54.0	69.6	0.18 vs. 0.54
0–8 vs. ≥ 9	29.8	48.6	74.3	122.9	55.1	69.0	0.19 vs. 0.56
0–9 vs. ≥ 10	27.9	46.5	76.6	123.1	56.3	68.8	0.20 vs. 0.57
0–10 vs. ≥ 11	21.4	41.0	85.6	126.6*	64.8	69.1	0.22 vs. 0.91
0–15 vs. ≥ 16	5.9	13.9	97.7	111.6	80.0	63.6	0.28 vs. 0.77

^a ^sum of sensitivity + specificity; * maximum Σ; PV+ positive predictive value; PV- negative predictive value; P_falls _probability of recurrent falls in low risk versus high risk group. The sample used in LASA to develop the fall risk profile included relatively healthy community dwelling older persons of which a large part reported zero previous falls [16]. In contrast, all participants of this study have a history of at least one recent fall and also include people living in a home for the elderly. Thus, the participants in our study are expected to have poorer mobility and more functional limitations and, on average, to score higher on the risk profile. The diagnostic values presented here are the recalculated values using the data of 426 independently living participants of the LASA study who fell at least once [16].

Fall history is assessed with the fall history instrument (Carefall Triage Instrument, version 007), which is a questionnaire developed by the Academic Medical Center, the VU University Medical Center and the Erasmus Medical Center, The Netherlands. The fall history collects data on the circumstances of the last and previous falls, mobility and risk factors of bone loss and osteoporosis, social status and general health. Medical history is assessed using a questionnaire on self-reported (chronic) diseases both in the past and present. The questionnaire includes 7 major chronic diseases, i.e. chronic lung diseases, cardiac diseases, vascular diseases, stroke, diabetes mellitus, malignant neoplasms and joint disorders (i.e. osteoarthritis and rheumatoid arthritis). In addition, participants are asked to indicate any other chronic disease, including psychological diseases, which they have or have had. Medication use is assessed by directly copying the names of drugs used in the previous two weeks from the containers. The name, doses per unit, number of times taken per day, time of administration, doses per intake, purpose, prescription or over the counter (OTC) and whether the drug has been prescribed after the fall are assessed for each drug. This information is compared to medication records of the public pharmacy. Level of independence in activities of daily living (ADL) will be examined using the Barthel Index (range 0, fully dependent, to 20, fully independent) [33]. The level of functioning on more complex daily activities will be examined using a scale of instrumental ADL introduced by Lawton and Brody (range 0, fully dependent, to 8, fully independent) [34]. Quality of Life (QoL) is examined using the Dutch translations of the SF-12 and the EQ-5D. The SF-12 consists of 12 items and is a abbreviated version of the SF-36 [35]. The SF-12 has been designed and validated to measure health related QoL in large population studies [35,36]. The EQ-5D (EuroQol) has been developed to generate a general index of experienced health and for the assessment of Quality Adjusted Life Years (QALY). It is therefore suitable for economic evaluations [37]. The assessment consists of 5 items (mobility, self-care, usual activities, pain/discomfort and anxiety/depression) and a visual analogue scale (0, worst, to 100, best imaginable health state) [37]. The fall history, ADL and QoL questionnaires are sent to the participants prior to the first home visit. Participants are asked to complete these questionnaires before the home visit. The visiting researcher assists participants who are unable to complete these questionnaires independently.

To assess physical performance, four tests are conducted (see Figure 2). The chair stands test is a standardized test in which the participant stands up and sits down for five consecutive times as fast as possible with the arms folded in front of the chest [38]. During the walk test the participant walks 3 meter along a line, turns 180 degrees and walks 3 meters back along the line [38]. Time is recorded in both tests from start to finish. The functional reach is a standardized test to measure the ability to maintain balance while reaching forward [39]. The participant stands parallel to a wall with one arm horizontally stretched and then leans forward while keeping the arm stretched and horizontal. The distance between the start and end position of the index finger is measured in centimetres. The modified Romberg test is used as a measure for standing balance. The participant stands consecutively with the feet apart at shoulder width, with the feet side to side, with one foot in front of the other but not in one line and with the feet in one line and heel against toe (tandem stand). All positions are performed first with the eyes open and then with the eyes closed. The participant scores 1 point per position continued for at least 10 seconds (range 0, poor balance, to 4, good balance) [40].

